**(Methods)**

1. The study design

This is a randomized, double-blind, placebo-controlled study. The patients will be recruited in the University Hospital of the State University of Campinas. The trial will be explained to all patients, and their written informed consent will be obtained before any trial-related procedures initiates.

2. Eligibility

Eligible patients are 18 to 80 years-old, both male and female patients with type 1 or type 2 diabetes mellitus with established diagnosis for more than 2 years, and with wounds that were difficult to be healed for at least three months. The probands should also have serum creatinine below 1.5mg/dL.

3. Exclusion criteria

Patients will be excluded if they do not satisfy the inclusion criteria, if the wounds are infected, if cellulites, venous stasis, inadequate perfusion and osteomyelitis are present, and if the patients are unable to attend the follow-up.

4. Informed consent

Patients who are eligible and not excluded according to the exclusion criteria described above will be informed of the background, purpose, method, spontaneous participation, withdraw rights of the study, and gave written consent. Study subjects can read this protocol if necessary.

5. Interventions

Patients who meet the criteria and seen between January 2004 and September 2007 will be considered for the study.

Group I intervention will consist of debridement for the ulcer, administration of the insulin cream (patent number: PI 0705370-3, University of Campinas, Brazil) on the wound, digital photograph by the same observer with the same camera (Sony, Cybershot, 8.1 megapixels) and measurement of the wound (height (↕) x width (↔) weekly, during 8-12 weeks. Group P intervention will consist of debridement for the ulcer, administration of the placebo cream on the wound, digital photograph by the same observer with the same camera (Sony, Cybershot, 8.1 megapixels) and measurement of the wound (height (↕) x width (↔) weekly, during 8-12 weeks.

Blood will be collected in both groups, in order to perform laboratory analysis, such as leukocyte count, hemoglobin, platelet count, glucose, creatinine, and glycosylated hemoglobin. These analyses will be made in the University Hospital of State University of Campinas, in the routine laboratory.

The detailed schedule is shown in the Table 1

Table 1. Schedule of the study

| Visit | Blood Sample | Digital  Photograph | Size of the wound height (↕) x width (↔) | Group I | Group P |

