| --- | --- | --- | --- | --- | --- |
| 1 |  |  |  | Active | Placebo |
| 2 |  |  |  | Active | Placebo |
| 3 |  |  |  | Active | Placebo |
| 4 |  |  |  | Active | Placebo |
| 5 |  |  |  | Active | Placebo |
| 6 |  |  |  | Active | Placebo |
| 7 |  |  |  | Active | Placebo |
| 8 |  |  |  | Active | Placebo |

6. Target sample size

Target sample size is 46, which corresponds to the number of patients that attended the inclusion criteria.

7. Administration of the investigatory product (IP)

The insulin or the placebo cream will be administrated according to the schedule table shown in Table 1.

8. Investigatory product

The insulin cream used is prepared with regular insulin (0.5U/g cream) in the pharmacy of our University Hospital and holds the patent number, PI 0705370-3 (University of Campinas, Brazil). In preliminary experiments, we used different concentrations of insulin to prepare the cream, but the doses that induced the best effect in wound healing without changing blood glucose was 0.5U/g. The cream under study, vehicle or with insulin, is applied locally to cover the excision.

9. Randomization

Eligible participants will be provided unique subject identification numbers according to study criteria and will be assigned to the insulin cream group or to the placebo group by a research technician ([name]), according to a computer-generated, randomization plan.

10. Limitation and fixation of concomitant medication

The oral drugs or s.c. insulin used by the patients to treat diabetes will not be changed during the treatment period with placebo cream or insulin cream, that will be at least 8 weeks.

11. Analysis

Primary outcome measure:

% of Wound healing closing measured each week [Time Frame: 7 days ] [ Designated as safety issue: Yes ].

Secondary outcome measure:

Complete wound healing [Time Frame: 8 weeks] [Designated as safety issue: Yes ]

Safety analysis

The prevalence of adverse events will be compared between the insulin and the placebo cream interventions.

12. Statistical analysis

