Wound dimensions will be calculated in a blinded fashion and analyzed for homogeneity and significance using the SPSS, version 13.0 (SPSS, Inc., Chicago, IL, USA). All continuous variables will be expressed as means  SE. One-way analysis of variance (ANOVA) will be used to assess the differences in a continuous variable between the two groups of patients. Post hoc analysis was performed using Tukey’s test. All tests will be two tailed, and the level of significance employed will be *P*<0.05.

[Response to adverse events]

In case of adverse events escalation of the investigatory product should be discarded, the investigatory product should be de-escalated or ceased if necessary. Adverse events should be reported to the principal investigator and the study supervisor.

[Handling of study data]

Data will be collected and fixed by the principal investigator. Data will be analyzed after key-open.

[Registration of the study]

The study will be registered in ClinicalTrials.gov.

[Publication of the study]

The study will be published to the journal under the names of the investigators,

or the name of study group if necessary.

ADDENDUM 1.

The form that will be fulfilled in the hospital follows the model below:

Name:_____________________________________________ Number:_____

Birthday date:­­­­­­­­­­­­­­­­___________________________________________________

Gender: □ Male □ Female

□ Type 1 diabetes □Type 2 diabetes Time after the diagnosis:_________

Time of wound:_________________ Wound location:____________________

Wound size:___________________ cm

Signs of infections: □ Yes □ No

Cellulitis: □ Yes □ No

Inadequate perfusion: □ Yes □ No

Osteomyelitis: □ Yes □ No

Beginning of the treatment:__/__/____ □ Insulin Cream □ Placebo

Serum creatinine:________________mg/dL

Weekly evaluation:

__/__/____ Wound size area:_______________cm (height (↕) x weidth(↔))

Aspect of the wound:________________________

Signs of infections: □ Yes □ No

Cellulitis: □ Yes □ No

Inadequate perfusion: □ Yes □ No

Osteomyelitis: □ Yes □ No

Weekly reduction of the wound area: ___________cm (height (↕) x weidth(↔))

Have photographs been taken? □ Yes □ No

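### Laboratory glucose is collected but not named in the safety analysis; the only rule reaching it, mean and SE with a one-way ANOVA, shows no individual low values.

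*Combined protocol and SAP*

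**What the plan says.** Four places in the combined protocol and SAP bear on this.

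- **Section 5 (Interventions)** has blood drawn in both groups for laboratory analyses, "such as leukocyte count, hemoglobin, platelet count, glucose, creatinine, and glycosylated hemoglobin".
- **Section 8 (Investigatory product)** explains the strength of the cream: in preliminary experiments "the doses that induced the best effect in wound healing without changing blood glucose was 0.5U/g".
- **Section 11 (Analysis)** gives the whole safety analysis in one sentence: "The prevalence of adverse events will be compared between the insulin and the placebo cream interventions". It names no laboratory value, and the term adverse event is not defined anywhere in the document.
- **Section 12 (Statistical analysis)** gives one rule for continuous data. "All continuous variables will be expressed as means" with their SE, and "One-way analysis of variance (ANOVA) will be used to assess the differences in a continuous variable between the two groups of patients". The section opens with wound dimensions and does not mention glucose.

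Two other provisions matter. Section 10 keeps the patient's diabetes drugs unchanged during treatment. The form in Addendum 1 has a field for serum creatinine but none for glucose or adverse events.

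**The concern.** The product under test contains insulin and is applied to an open wound. By its own reason for choosing the strength, the plan treats blood glucose as the systemic quantity to watch. It collects that quantity and then gives it no place in the safety analysis. What remains is the default for any continuous variable.

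A mean and SE per arm, with one test of the difference, gives no minimum, no count below a limit and no within-patient change. If a small number of patients on the insulin cream had low values, this summary would absorb them. At this sample size, a non-significant difference in means would also say little about whether glucose was affected. At stake is the safety statement about glucose. The two stated outcomes, percentage closure and complete healing, are not affected.

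**Working it through.** **Inputs from the document.** The total sample size is 46, given as a count of eligible patients: "Target sample size is 46, which corresponds to the number of patients that attended the inclusion criteria". There is no power calculation to reproduce. Tests are two-sided at 0.05 (Section 12).

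**Assumed inputs (the document gives none).** Equal allocation, so 23 per arm; Section 9 says only that assignment is "according to a computer-generated, randomization plan". Between-patient glucose SD 60 mg/dL, range 40 to 80. Affected patients fall by 100 mg/dL; 2 or 3 of the 23 on insulin cream are affected, and none on placebo.

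**Step 1. Shift in the arm mean** = k × 100 / 23.
- k = 2: 200/23 = 8.7 mg/dL
- k = 3: 300/23 = 13.0 mg/dL

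**Step 2. SE of the difference** = SD × √(2/23).
- SD 40: 11.8; SD 60: 17.7; SD 80: 23.6 mg/dL

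**Step 3. Chance that the ANOVA gives P<0.05.** With two groups the ANOVA is the two-sample t-test. Power comes from the noncentral t distribution with 44 df and noncentrality shift/SE (8.7/17.7 = 0.49 for k = 2 at SD 60).

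| SD (mg/dL) | 2 of 23 affected | 3 of 23 affected |
| --- | --- | --- |
| 40 | 11.1% | 19.1% |
| 60 | 7.7% | 11.1% |
| 80 | 6.5% | 8.4% |

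The false-positive rate is 5%. These figures flatter the ANOVA, because they ignore the extra variance that the falls themselves create. Simulating the falls (40,000 runs per setting) gives about 6.0% (5.7% to 7.4%) for 2 patients and 8.5% (6.8% to 11.4%) for 3.

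**Step 4. Low values instead of falls.** A fall of 100 mg/dL need not end in a low value, so a second scenario sets the affected patients to 50 mg/dL, with arm means of 150 to 180 mg/dL, SD 40 to 80 and all other values at or above 70 (all assumed). By simulation the ANOVA gives P<0.05 in 6% to 8% of trials with 2 such patients and 9% to 15% with 3. The conclusion is the same.

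**Step 5. What a non-significant result would exclude.** The 95% CI half-width is t(0.975, 44) × SE = 2.015 × SE.
- SD 40: 23.8; SD 60: 35.7; SD 80: 47.5 mg/dL

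An interval of about ±24 to ±48 mg/dL cannot support a statement of no change.

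**Step 6. What the alternatives gain.**
- *Count of patients below a limit.* 2/23 = 8.7% (exact 95% CI 1.1% to 28.0%); 3/23 = 13.0% (2.8% to 33.6%). Fisher's exact P against 0/23 is 0.49 and 0.23, and first drops below 0.05 at 5/23 (P = 0.049).
- *Baseline adjustment.* With an assumed baseline correlation of 0.7, the residual SD is 60 × √(1 − 0.49) = 42.8 and the SE is 42.8 × √(2/23) = 12.6. Power becomes about 10% for 2 patients and 17% for 3, against 8% and 11% unadjusted.

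Neither makes a few cases statistically significant. The count and the listing put each case on the page.

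**The case against.** The strongest reply is that Section 12 never mentions glucose, so the plan cannot be charged with choosing an ANOVA for it. This is fair as to wording: no glucose analysis is specified, and the ANOVA applies only as the default for continuous variables. It does not remove the gap. If the default does not reach glucose, then glucose has no planned analysis at all, and the remedy is the same.

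Second, a low value could still be counted through the adverse-event comparison. That stands, and it would be wrong to say that such cases could never appear. But without a definition, a threshold or a field on the form, nothing ensures that a low laboratory value is recorded as an event.

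Third, a reader might infer that absorbed insulin would affect a few patients rather than shift the whole arm, so that a comparison of means is simply the wrong scale. The documents say nothing on this. A modest shift across the arm is equally possible, and means do address that.

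Fourth, a reader might infer that the trial is set to announce that the cream has no effect on glucose. No such statement is planned. The remark on unchanged glucose in Section 8 describes preliminary experiments and is not a hypothesis of this trial.

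Fifth, lowest values and changes from baseline need repeated samples. The blood-sample cells of Table 1 are blank in the extracted text, where marks may have been lost, so the schedule cannot be confirmed and no criticism is made of it. It cannot be assumed that every proposed summary is available from blood already drawn. Timing relative to food and to cream application is not stated either, so a scheduled sample could miss a brief low. Fixed diabetes drugs remove one source of glucose change, but not diet or day-to-day variation.

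**Conclusion.** The concern holds in a limited form. Glucose is collected and is the systemic measure that the plan itself links to the cream, but the safety analysis does not name it. The only rule that reaches it gives arm means, which do not display individual low values.

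Under the stated assumptions the ANOVA would flag 2 affected patients about 6.5% to 11% of the time and 3 about 8% to 19%, and the interval for the mean difference would extend about 24 to 48 mg/dL either side. The allocation ratio, SD, size of fall and number affected are all assumptions; the conclusion holds across the range tried. The change should be made because the default gives a weak safety readout for an insulin product and a better one is cheap. The documents do not show that low values would go unreported, or that a false claim of safety is planned.

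**What to change.** In Sections 11 and 12:

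1. Name laboratory glucose in the safety analysis.
2. From the samples that the blood schedule provides, report by arm the number and percentage of patients below a limit that the investigators set before unblinding, with an exact 95% CI, and list each patient's lowest value.
3. Where both baseline and on-treatment samples exist, replace the raw ANOVA of glucose with the between-arm difference adjusted for baseline glucose, with its 95% CI.
4. State that absence of an effect on glucose will not be inferred from P>0.05.

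The choice of limit is a clinical matter for the investigators. The cost is a few sentences and one extra table. The trial may also have to report a wide interval. Whether any further blood sampling would be needed depends on the schedule in Table 1, which should be checked first.

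### The plan does not require its open analysis choices to be settled before the treatment key is opened, and the patient form shows the arm beside the weekly readings

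*Combined protocol and SAP*

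**What the plan says.** The section 'Handling of study data' consists of two sentences: "Data will be collected and fixed by the principal investigator" and "Data will be analyzed after key-open". It does not mention a dated lock, a completed analysis plan or a holder of the key.

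On blinding, Section 1 states "This is a randomized, double-blind, placebo-controlled study" without listing who is blinded. Section 12 adds "Wound dimensions will be calculated in a blinded fashion", and this is the only step of data processing or analysis that is said to be blind. Under Section 9 a research technician assigns patients "according to a computer-generated, randomization plan".

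The form in Addendum 1 carries the line "Beginning of the treatment:__/__/____ □ Insulin Cream □ Placebo". The same form holds the weekly wound size, the weekly reduction in area, and the repeated infection and perfusion entries.

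Section 11 defines the primary outcome as the percentage "of Wound healing closing measured each week [Time Frame: 7 days" and gives complete healing at 8 weeks as the secondary outcome.

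**The concern.** Opening the key before the comparative analysis does little harm when the analysis is fully specified, because knowing the arms then changes nothing. Here several decisions that affect the result are still open when the key opens. Someone who knows which patients received insulin could settle them, knowingly or not, by looking at which option shows a difference.

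The tick box raises a related risk. If it is completed at the start of treatment, as its place beside the start date suggests, the arm can be read by anyone who handles the form while weekly entries are made and the data fixed. Blinding of the readings and of data corrections would then depend on practice that the plan does not describe.

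At stake are the credibility of the double-blind claim and the 5% error rate on the primary outcome.

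**Working it through.** **Step 1. What is settled and what is open**

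| Item | Where | Status |
|---|---|---|
| Test for continuous variables, two-sided tests, 0.05 level | Section 12 | Settled |
| Calculation of wound dimensions | Section 12 | Blind |
| Week for the primary comparison | Section 11: weekly measurement, 7-day time frame | Open |
| Primary variable | Section 11 gives percent closure; the form gives weekly reduction in area; no reference reading is stated | Open |
| Horizon | Section 5: 8 to 12 weeks; Table 1: 8 visits; Section 10: at least 8 weeks | Open |
| Test for complete healing (yes/no) | Section 12 names a test only for continuous variables | Open |
| Analysis set, missing readings, multiple testing | Not addressed | Open |
| Point by which the open items must be settled | Handling of study data | Not stated |

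**Step 2. Size of one open choice, the week**

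The plan gives no figure to reproduce here. Inputs from the documents are 46 patients (Section 6), weekly readings for 8 to 12 weeks (Section 5) and two-sided 0.05 (Section 12). Three things are assumed because the documents do not give them: a 1:1 split (46 / 2 = 23 per arm), normally distributed outcomes, and the between-week correlation.

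If the weeks were independent, the chance of at least one significant week with no true effect would be 1 − (1 − 0.05)^k:

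- k = 8: 1 − 0.95^8 = 33.7%
- k = 12: 1 − 0.95^12 = 46.0%

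Readings on the same wound are correlated, so these are ceilings. For correlated weeks, 40,000 trials with no effect were simulated. Each week was tested with the two-sample t-test, which for two groups is the same as one-way ANOVA (F = t², 44 degrees of freedom):

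| Weeks | Correlation pattern | 0.9 | 0.7 | 0.5 |
|---|---|---|---|---|
| 8 | Equal between all weeks | 12.0% | 19.3% | 25.2% |
| 8 | Declining with distance (AR(1)) | 16.4% | 24.9% | 30.0% |
| 12 | Equal between all weeks | 13.4% | 23.8% | 32.4% |
| 12 | Declining with distance (AR(1)) | 21.6% | 34.9% | 41.3% |

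Simulation error is about 0.2 percentage points: √(0.25 × 0.75 / 40,000) = 0.0022. With one week fixed in advance the rate is 5%.

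**Step 3. Limits of the illustration**

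The rates count a significant week in either direction. They measure free choice of week, and that inflation occurs whether the arms are labelled or coded. Knowing the arms adds the ability to choose in a preferred direction. If visit 1 is the baseline, 8 visits give 7 later readings, and the independent-weeks ceiling falls to 1 − 0.95^7 = 30.2%.

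**The case against.** The case for leaving the text as it stands has real force on several points.

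- **The order is normal.** 'Fixed' most naturally means finalised, and it comes before key-open. This stands: analysing after key-open is not an error in itself. But fixing the data does not fix the analysis, and the plan neither says what is fixed nor states outright that fixing comes first.
- **Much is already set.** The test for continuous variables, the sidedness and the significance level are stated, and wound dimensions are calculated blind. This stands, so the point covers only the items left open.
- **The 7-day time frame could be read as naming week 1.** The same line says the outcome is measured every week, so it does not settle the matter.
- **The tick box could be filled in only after key-open.** This is possible, since the documents do not say when it is completed. The supportable statement is that the arm may be visible, not that it is.
- **Neutral codes do not stop selection of a favourable week.** This stands, so the fix must also name the open choices.

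A reader might infer four stronger things that the documents do not support:

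- *Patients can be excluded once the arms are known.* The grounds in Section 3 are entry criteria. Sections 4 and 9 apply them before consent and assignment. The weekly form records infection and perfusion again, but no rule ties those entries to removal from the analysis. No error rate for selective exclusion should therefore be attached to this plan.
- *The principal investigator knows the arms while fixing the data.* The text does not show this; it only fails to exclude it.
- *All analysis decisions rest with that one role.* The plan does not say who analyses the data.
- *The data file reveals the arms through the labels Group I and Group P.* No section says the file carries those labels, and Section 9 gives patients identification numbers.

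**Conclusion.** The concern holds in a limited form. The plan places analysis after key-open and does not require the open choices (primary week and variable, 8 or 12 weeks, analysis set, test for complete healing) to be settled beforehand. The only data-processing step stated to be blind is the calculation of wound dimensions, and the patient form may show the arm while the data are being fixed.

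For the choice of week alone, the false-positive rate could be about 12% to 25% instead of 5%, which is 2.4 to 5 times nominal. This rests on 8 weekly tests, 23 patients per arm, no true effect, and an equal between-week correlation of 0.9 to 0.5, all assumed except the 46 patients, the weekly schedule and the 0.05 level. It shows what the text permits and is not an estimate of what was done. The change is worth making because the protection is cheap and the gap bears on the primary outcome.

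**What to change.** 1. In Addendum 1, replace the insulin or placebo tick box with a subject or kit code.

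2. Replace the sentence on analysis after key-open with:

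> One primary week and variable, the analysis set and the test for complete healing are fixed in a dated analysis plan, and the data are locked with a dated sign-off, before the key is opened. The primary, secondary and safety analyses are run on neutral codes (A/B), then the holder of the randomisation plan opens the key. Any later change is reported as post hoc.

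The analysis plan should also state the horizon it uses, how missing readings are handled, and how the weekly readings outside the primary week are treated. Sections 5 and 10 and Table 1 differ on the length of the treatment period and must be reconciled by the sponsor. No view is taken here on which length is right.

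The cost is one paragraph, one form edit and a dated lock record. The role that holds the key has to be named, since the documents do not name it.

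### The model hospital form has a named-arm tick box above the weekly wound fields, which conflicts with the stated blinding and puts the primary outcome at risk of assessment bias

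*Combined protocol and SAP*

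**What the plan says.** Three statements in the protocol set up the blind. Methods 1 (study design) says "This is a randomized, double-blind, placebo-controlled study". Section 12 (Statistical analysis) says "Wound dimensions will be calculated in a blinded fashion". The paragraph on handling of study data says "Data will be collected and fixed by the principal investigator. Data will be analyzed after key-open", which implies a code that hides the arm until the data are fixed.

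Section 9 (Randomization) gives each participant a unique identification number. It says that participants "will be assigned to the insulin cream group or to the placebo group by a research technician", working from a computer-generated plan.

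Addendum 1 then supplies the data collection instrument, introduced with "The form that will be fulfilled in the hospital follows the model below". The line that takes the treatment start date also carries the choice "Insulin Cream □ Placebo". Below it comes the weekly evaluation block: wound area as height by width, aspect of the wound, signs of infection, cellulitis, perfusion, osteomyelitis, weekly reduction in area, and whether photographs were taken. The form already has a number field at the top.

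**The concern.** A form designed for a blinded trial would identify the patient by a code and leave the arm elsewhere. This one asks for the arm by name, next to the date on which treatment starts and above the fields that hold the outcome. Read in the ordinary way, the box is filled in on day one and stays visible at each later visit.

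Both efficacy outcomes depend on an observer. Percentage closure comes from a height and a width that someone measures, and complete healing is a judgement. If that person knows the arm, small and unintended differences in where the wound edge is taken to lie can add up to an apparent treatment difference. No later analysis can separate such a difference from a real effect, so a positive result would be open to the charge of assessment bias.

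**Working it through.** **Setting the passages side by side**

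| Question | What the documents say |
| --- | --- |
| Is the trial blinded? | Yes, double-blind (Methods 1) |
| Is wound measurement blinded? | The dimensions are to be calculated blind (Section 12); the assessor and the mechanism are not described |
| When is the arm revealed? | At key-open, before analysis (Handling of study data) |
| Who handles the data before then? | The principal investigator collects and fixes them (same paragraph) |
| Where is the arm written? | In a named-arm box on the treatment-start line of the form (Addendum 1) |
| Where are weekly outcomes written? | Lower on the same model form (Addendum 1) |
| Who ticks the box, and when? | Not stated |
| Is the box left blank until key-open, or kept on a separate sheet? | Not stated |
| Do the analysed dimensions come from the form or from the photographs? | Not stated |

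The first three rows require the arm to be hidden until the data are fixed. The form asks for the arm at a point whose natural timing is the start of treatment. No instruction resolves the difference. The box is not needed to identify the patient, because the form has a number field and Section 9 provides unique subject numbers.

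**How much a measurement shift would matter**

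The plan has no figure of its own to reproduce here. The target of 46 in Section 6 comes without a power, SD, effect size or allocation ratio. The following is therefore an illustration.

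- From the documents: 46 patients in two groups; two-sided 5% level (Section 12).
- Assumed: 1:1 allocation, so n = 46/2 = 23 per arm; SD of percentage closure 25 or 30 points; no true effect; an average measurement shift b of 1, 2, 5 or 10 points in favour of one arm.

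One-way ANOVA with two groups is equivalent to the two-sample t-test, so that test is used.

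1. Standard error of the difference: SE = SD × √(2/23). This is 7.37 points for SD 25 and 8.85 points for SD 30.
2. Degrees of freedom: 46 − 2 = 44; critical value 2.015.
3. Noncentrality: δ = b/SE.
4. False-positive rate: P(|T| > 2.015), where T is noncentral t with 44 degrees of freedom and noncentrality δ.

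| Shift b (points) | δ, SD 30 | Rate, SD 30 | δ, SD 25 | Rate, SD 25 |
| --- | --- | --- | --- | --- |
| 1 | 0.11 | 5.1% | 0.14 | 5.2% |
| 2 | 0.23 | 5.6% | 0.27 | 5.8% |
| 5 | 0.57 | 8.6% | 0.68 | 10.2% |
| 10 | 1.13 | 19.8% | 1.36 | 26.4% |

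A shift of 1 or 2 points does almost no harm. A shift of 5 points roughly doubles the nominal error, and 10 points raises it four- to fivefold. The table covers one comparison of a continuous measure, not complete healing.

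**The case against.** A reader might infer that the double blind is actually broken for whoever measures the wound. The documents do not support that.

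- **The box is blank.** Addendum 1 is a blank model with an empty choice, not a record of any patient's arm. Nothing says who ticks it or when. Completing it at key-open would be compatible with the data-handling paragraph.
- **The sheet may not be shared.** The model shows one weekly block for at least eight weekly visits, so the block must be repeated or continued. Whether it shares a page with the treatment-start line cannot be told from the text.
- **The measurer may not use the form.** Section 12 promises blinded calculation, and the interventions section provides weekly photographs by one observer. The analysed dimensions could come from a blinded reading of those photographs.
- **The technician shows no unblinding.** Allocating from a list exposes nobody else unless that person also treats or measures, and the documents do not say so.
- **The error rates are not estimates.** SD, allocation and bias size are all assumed, and small shifts leave the error close to 5%.

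All of this stands against the claim of an actual break. It does not remove the inconsistency. The box sits with the start date, which points to completion then, and no text tells anyone to leave it blank. The form itself holds the weekly areas from which percentage closure follows, and no separate reader is described. The principal investigator would handle the forms before key-open whichever way the wounds are read.

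**Conclusion.** The concern holds as an inconsistency and a risk. Addendum 1 asks for the named arm on the form that also takes the weekly outcomes. The study design, Section 12 and the data-handling paragraph all require the arm to be hidden until the data are fixed. Completed as laid out, the form would show the arm early to those recording outcomes on it and to the principal investigator. Because this is a contradiction in the trial's own instrument and not merely a missing detail, it should be corrected.

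Confidence is high for the inconsistency. Whether the blind would fail in practice is unknown, because it depends on who fills in the box, when, and where the analysed dimensions come from. The possible inflation of the false-positive rate runs from negligible (about 5% for a 1-point shift) to serious (20–26% for a 10-point shift) under the assumed 23 per arm and SD of 25 to 30 points. The documents give no basis for choosing a value in that range, and the conclusion does not depend on one.

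**What to change.** 1. In Addendum 1, delete the named-arm tick box and put in its place a single field for the subject or cream code number.
2. State that the arm is kept only in the separate randomization list until the data are fixed and the key is opened.
3. State who measures the wound, whether the analysed dimensions come from the form or the photographs, and that the measurer and the principal investigator see codes only until then.
4. State that the allocating technician neither treats patients nor measures wounds. With that condition the technician can remain the allocator. Having the hospital pharmacy hold the list is an option, not a requirement.

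The cost is one line on the form and a few sentences in Sections 9 and 12 and the data-handling paragraph, plus code labels on the cream if these are not already in use. The sample size and visit schedule do not change. The one practical demand is that allocation be kept apart from treatment and measurement, which may need a check on who does what.
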